#### Inclusion criteria

Age < 30 daysSigned informed consent obtained from parent(s) or representative(s)

#### Exclusion criteria

Inability to acquire a diagnostic echocardiogramWeight less than 1.5 Kg

### Study tool

Cardiac sounds will be recorded using the Littmann Core Stethoscope (Eko Software) (3 M Company, Minnesota/USA). Digital recordings will be stored as wav files in a dedicate encrypted platform for data sharing among centres.

Each newborn enrolled in the study will undergo a standardized and complete echocardiogram by experienced operators as reported in *Table 1* and in the full Study Protocol submitted as Online Supplementary Material. Echocardiographic evaluation will be performed according to existing guidelines for neonatal echocardiography (please refer to the study protocol submitted as Online Supplementary Material for further details).^32^ SHD will be categorized based on the European Society of Cardiology classification system (simple, moderate and severe anatomical complexity), see Supplementary material online, *Table S2*.^33^ Exams will be performed with standardized and reproducible approach (*Table 1*). They will be stored on a digital support. After anonymization, the exams will be transferred to the Echocardiographic Study Core Imaging Laboratory for formal assessment and adjudication.

**Table 1 ztag103-T1:** Standardized nomenclature, timing, and imaging views for echocardiographic evaluation

Measurement	Timing	View(s)
**TV annulus**	Diastole	Apical 4-chamber
**Pulmonary valve annulus**	Systole	PSAX/PLAX
**Main pulmonary artery**	Systole	PSAX/PLAX
**Left/right pulmonary artery**	Systole	PSAX/PLAX
**Left atrial diameter**	Diastole	PLAX
**MV annulus**	Diastole	PLAX
**MV annulus**	Diastole	Apical 4-chamber
**Aortic root**	Systole	PLAX
**Ascending aorta**	Systole	SSN
**Transverse aortic arc**	Systole	SSN
**Aortic isthmus**	Systole	SSN
**Left ventricular diastolic/systolic area**	Diastole/Systole	Apical 4-chamnber
**Right ventricular diastolic/systolic area**	Diastole/Systole	Modifed apical 4-chamnber
**Left ventricular diameter**	Diastole	PLAX
**Left ventricular diameter**	Systole	PLAX
**TV E wave velocity**	Diastole	Apical 4-chamber
**TV A wave velocity**	Diastole	Apical 4-chamber
**TV deceleration time**	Diastole	Apical 4-chamber
**RV IVRT**	Diastole	Apical 4-chamber
**TV mean gradient**	Diastole	Apical 4-chamber
**TV regurgitant jet velocity**	Diastole	Apical 4-chamber
**RV outflow peak gradient**	Systole	PSAX
**RV outflow mean gradient**	Systole	PSAX
**RV outflow VTI**	Systole	PSAX
**Pulmonary valve peak gradient**	Systole	PSAX
**Pulmonary valve mean gradient**	Systole	PSAX
**Pulmonary valve VTI**	Systole	PSAX
**Left/right branch pulmonary artery peak gradient**	Systole	PSAX
**Left/right branch pulmonary artery mean gradient**	Systole	PSAX
**Left/right branch pulmonary artery VTI**	Systole	PSAX
**MV E wave velocity**	Diastole	Apical 4-chamber
**MV A wave velocity**	Diastole	Apical 4-chamber
**MV deceleration time**	Diastole	Apical 4-chamber
**LV IVRT**	Diastole	Apical 4-chamber
**MV mean gradient**	Diastole	Apical 4-chamber
**MV regurgitant jet velocity**	Diastole	Apical 4-chamber
**MV peak gradient**	Diastole	Apical 4-chamber
**MV mean gradient**	Diastole	Apical 4-chamber
**MV outflow VTI**	Diastole	Apical 4-chamber
**Aortic valve peak gradient**	Systole	Apical 5-chamber
**Aortic mean gradient**	Systole	Apical 5-chamber
**Aortic regurgitant jet velocity**	Systole	Apical 5-chamber
**Aortic valve pressure half-time**	Systole	Apical 5-chamber
**Aortic valve VTI**	Systole	Apical 5-chamber
**Aortic arch peak gradient**	Systole	SSN
**Aortic arch mean gradient**	Systole	SSN
**Aortic arch VTI**	Systole	SSN
**Lateral LV E’ wave TDI**	Diastole	Apical 4-chamber
**Lateral LV A’ wave TDI**	Diastole	Apical 4-chamber
**Septal LV E’ wave TDI**	Diastole	Apical 4-chamber
**Septal LV A’ wave TDI**	Diastole	Apical 4-chamber
**RV free wall E’ wave TDI**	Diastole	Apical 4-chamber
**RV free wall A’ wave TDI**	Diastole	Apical 4-chamber

MV, mitral valve; PLAX, parasternal long AXis; PSAX, parasternal short AXis; RV, right ventricle; SSN, SupraSternal notch; TDI, tissue Doppler imaging; TV, tricuspid valve; VTI, velocity time integral.

A web-based, encrypted Case Report Form will be created using the institutional REDCap (Vanderbilt University) license of IRCCS Azienda Ospedaliero-Universitaria di Bologna.

### Study procedure

#### Patient enrolment

For the derivation phase newborns without SHD will be enrolled at the time of discharge from Ob/Gyn programme and newborns with SHD will be enrolled at the time of cardiovascular examination. For the validation phase consecutive newborns will be enrolled at the time of discharge from Ob/Gyn unit.

*
Graphical abstract
* summarizes the study pipeline.

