### Study population

#### Derivation phase

Study population will include neonates with known cardiovascular status including newborns with and without SHD. Working definition of SHD is any cardiovascular anomaly that will require longitudinal follow-up or intervention based on current practice. This broad definition of SHD parallels the overall goal of this investigation: to develop a screening tool aiming for high sensitivity and flexible performance across the diverse and heterogeneous morphological and functional spectrum of cardiovascular anomalies in newborns.

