#### Derivation phase

After screening of eligible patients, written informed consent will be obtained from parents or caregivers.

The first echocardiographic evaluation will take place at a post-natal age < 30 days. Age at recording and echocardiographic evaluation will be planned not before 7 days of post-natal life to allow completion of proper cardio-circulatory transition in the healthy newborns (i.e. ductal closure, pulmonary vascular remodelling, foramen ovale physiologic shunt). The echocardiogram will be linked to an anonymous identifier which will be used to link the exam to the patient without breaching patient privacy. The examination will be digitally stored and transferred to the Echocardiography Study Core Lab for formal revision. The cardiovascular neonatal status will be appropriately labelled as being with or without cardiovascular abnormalities.

Heart sound will be digitally recorded using as acquisition device Littmann Core Stethoscope (Eko Software) (3 M Company, Minnesota/USA). Cardiac sound tracings will be recorded and stored in wav format and encrypted transferred to the Bioengineer Research Unit for further elaboration. Cardiovascular neonatal status will be un-blinded to the Bioengineer Research Unit to allow for proper handling of classifier training.

The details of the acquisition method are as follows:

Acquisition device: Littmann Core Stethoscope (Eko Software) (3 M Company, Minnesota/USA)No filtering of raw signal will be applied. Specifically, the Stethoscope filtering and volume equalization will be set at 0 through the Eko interface. The only residual filter will be the analogue filter related to the stethoscope membrane's elastic properties. This is to minimize the impact of the specificities of the Eko Software on the sound samples and therefore on the training of the classifier.Position of the auscultation: mid precordium, 1 cm medial and 1 cm above papilla mammae (see Online Supplementary Material). Gentle pressure is applied on chest, spontaneous breathing, patients will be kept as calm as possible using maternage without any sedation. Sound sampling will be performed in a calm environment (outpatient clinic or neonatal intensive care unit). A total of three recordings per patient are anticipated to improve sound quality. Sampling tracings with abnormal acoustic contamination (intense crying, environmental noises, friction rubs) will be discarded.Average recording duration: 15 s

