Phonocardiographic signals will be stored as wav files in an encrypted cloud system to be transferred for further analysis (*Graphical abstract*). Tracings will undergo preliminary processing to remove background noise, and will be segmented to generate sound samples of homogeneous suitable tuned duration. As the last step of the preprocessing, the filtered records will be normalized for preventing inhomogeneity in the extracted features. Data analysis will be then implemented based on handcrafted feature extraction. The main objective of feature extraction is to identify a small number of representative features characteristic properties of a sound sample, that replace the high-dimensional raw signals still preserving its informative content with respect to the phenomenon under investigation. Relevant features are then fed to the classification algorithm to discriminate between healthy and abnormal subjects. Multiple different techniques will be used for feature extraction in sound signals, and can be loosely grouped into frequency-domain techniques, time-frequency domain techniques, linear predictive coding, and time-domain techniques. Each of these techniques provides descriptors of potentially relevant properties of the sound sample, which can be used as features or further processed to extract higher level characteristics of the signal (such as systole and diastole variability). To maximize the robustness of our results to less-than-ideal acquisition conditions, we will train the classifiers using features from all the above-mentioned domains and will perform a feature selection procedure to select those features which are mostly correlated to the outcome of interest. Standard machine learning models will be preferred, as simpler models tend to perform more robustly when training data is limited. Neural networks may be implemented if they will exhibit superior results with respect to standard models on the available dataset without clear signs of overfitting. Following the standard best practice, the dataset will be split into training set, validation set and test data set. For evaluating the performance of classifiers, K-Fold cross-validation with different fold numbers will be used: 10-fold, 5-fold, and Leave-One-Out-Cross-Validation (LOOCV). In LOOCV, the number of folds is equal to number of records. Gini importance for Random Forest classifiers will be used as a tool to validate parameters with least predictive contribution. Once a proper classifier has been trained a post training analysis to determine the most relevant features will be conducted. The purpose of this analysis is to investigate to which extent each feature is contributing to the selection of one class with respect to the other. Techniques for feature relevance estimation based on SHAP values, or permutation analysis will be applied also with the aim of providing a proper explanation to the model decision (*Graphical abstract*).

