## Discussion

The DI_SOUND study is designed to develop and validate a digital classifier of neonatal cardiac sounds with the aim of improving the efficiency and effectiveness of screening for SHD in newborns. Current neonatal cardiovascular screening strategies rely on pulse oximetry (pre- and post-ductal oxygen saturation) combined with physical examination prior to discharge.^12–16^ While this approach has improved early detection of critical congenital heart disease, its diagnostic performance remains suboptimal, particularly in terms of sensitivity and operator dependency.^16^

Cardiovascular auscultation, historically a cornerstone of neonatal assessment, is inherently subjective and dependent on clinician experience.^14^ Several contemporary factors further limit its effectiveness. First, increasing prenatal detection of SHD has led to centralization of care, reducing exposure of general paediatric trainees and frontline providers to pathological cardiac findings, thereby potentially diminishing auscultatory proficiency.^35^ Second, early postnatal discharge (typically within 48–72 h) may occur before the full haemodynamic expression of certain defects, particularly those involving post-tricuspid shunts, due to persistently elevated pulmonary vascular resistance during transitional circulation. Third, the growing reliance on advanced diagnostic technologies may paradoxically reduce emphasis on meticulous physical examination skills.^35^ Collectively, these factors contribute to the persistence of false-negative screening results, which carry significant clinical risk.

Conversely, current screening strategies are also limited by suboptimal specificity, leading to a considerable number of false-positive cases. This results in unnecessary cardiology referrals, increased healthcare utilization, prolonged hospitalization, and heightened parental anxiety. Therefore, there is a clear unmet need for tools that can enhance both sensitivity and specificity while remaining accessible and scalable.

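### In the derivation phase the recruitment stream follows the SHD label, and the stated internal evaluation cannot show whether recording setting inflates the Aim 1 accuracy

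*Protocol article*

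**What the plan says.** All references are to the protocol article.

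- **Sampling.** Under Study population, Derivation phase: "Study population will include neonates with known cardiovascular status including newborns with and without SHD". Status is therefore known at enrolment.
- **Streams.** Under Patient enrolment: "newborns without SHD will be enrolled at the time of discharge from Ob/Gyn programme and newborns with SHD will be enrolled" when they have their cardiovascular examination. For Aim 2: "For the validation phase consecutive newborns will be enrolled at the time of discharge from Ob/Gyn unit".
- **Setting.** Under Study procedure, Derivation phase: "Sound sampling will be performed in a calm environment (outpatient clinic or neonatal intensive care unit"). Neither place is assigned to a group, and no balance between groups is stated.
- **Age.** The same section gives one window for everyone: "Age at recording and echocardiographic evaluation will be planned not before 7 days of post-natal life", and "The first echocardiographic evaluation will take place at a post-natal age < 30 days".
- **Feature choice.** The plan is to "perform a feature selection procedure to select those features which are mostly correlated to the outcome of interest".
- **Evaluation.** The same section and the Statistic plan describe a training/validation/test split and 10-fold, 5-fold and leave-one-out cross-validation. All of these lie inside the derivation data of 600 newborns (2:1 diseased to healthy). The targets are sensitivity above 95% and specificity above 90%. No fold is defined by centre or by setting.
- **Safeguards.** One stethoscope model with its filters off, one auscultation point, a calm environment, discarding of contaminated tracings, noise removal, normalization, and SHAP or permutation analysis after training.

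The Limitation section does not mention the two recruitment streams.

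**The concern.** The label and the route into the study are the same variable in this phase. If the route also affects where a newborn is recorded, any residual difference in background sound between a clinic room and an intensive care unit becomes associated with SHD. A selection step that keeps the features most correlated with the label has no means of telling such a feature from a cardiac one. Random folds carry the same association in training and test portions, so cross-validation would reward the feature.

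At stake is the credibility of the Aim 1 sensitivity and specificity, which decide whether a classifier goes forward. An optimistic figure would be discovered only in Aim 2, after recordings and echocardiograms in about 1,900 newborns. The derivation recordings could not be remade by then.

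**Working it through.** **1. The plan's own precision figure.** Inputs from the Statistic plan: 600 newborns at 2:1 gives 400 with SHD and 200 without; targets 95% and 90%. Half-width = 1.96 × √(p(1−p)/n).

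- Sensitivity: 1.96 × √(0.95 × 0.05/400) = 0.0214
- Specificity: 1.96 × √(0.90 × 0.10/200) = 0.0416

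The stated ±2% and ±4% are reproduced. They describe sampling error only. Bias from the two streams would not widen them.

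**2. Where would controls be recorded?** The Discussion gives "early postnatal discharge (typically within 48–72 h") as usual. Recording starts at day 7. A healthy newborn enrolled at discharge would therefore ordinarily be recorded after going home, which points to the outpatient clinic. NICU recordings would then come mainly from newborns with SHD. This follows from combining three statements; the article does not say it.

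**3. What setting alone could contribute.** For a yes/no rule, AUC = (sensitivity + specificity)/2. All NICU shares below are assumptions.

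| NICU share, SHD | NICU share, no SHD | AUC of a setting-only rule |
|---|---|---|
| 60% | 5% | (0.60 + 0.95)/2 = 0.775 |
| 30% | 5% | (0.30 + 0.95)/2 = 0.625 |
| 60% | 0% | (0.60 + 1.00)/2 = 0.80 |
| 30% | 0% | (0.30 + 1.00)/2 = 0.65 |

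**4. Would cross-validation notice?** A simulation used 400 newborns with SHD and 200 without, one heart-sound feature, and one background feature shifted by 4 SD in recordings that carry a setting signature. The model was ridge logistic regression with 10-fold cross-validation, over 100 runs. Each fitted model was then applied to a sample in which both groups had the controls' share of the signature. The shares and the shift are assumptions.

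| Signature share, SHD / no SHD | Heart feature | 10-fold AUC | Sensitivity at 90% specificity (10-fold) | AUC with equal setting |
|---|---|---|---|---|
| 20% / 20% | none | 0.47 | 0.08 | 0.50 |
| 40% / 0% | none | 0.70 | 0.46 | 0.50 |
| 70% / 0% | none | 0.84 | 0.73 | 0.50 |
| 95% / 10% | none | 0.92 | 0.86 | 0.50 |
| 20% / 20% | 1 SD | 0.76 | 0.39 | 0.76 |
| 40% / 0% | 1 SD | 0.83 | 0.57 | 0.73 |
| 70% / 0% | 1 SD | 0.90 | 0.77 | 0.71 |
| 95% / 10% | 1 SD | 0.94 | 0.90 | 0.64 |

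With equal shares there is no false gain. With unequal shares, cross-validation reports a gain that disappears once setting is equalised. The 4 SD shift represents a strong residual signature; effective noise removal would make the effect smaller.

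**The case against.** **Place of enrolment is not place of recording.** This is correct. The article gives one list of settings for the whole phase, so the link between setting and label is an inference. Step 2 makes it likely but does not establish it.

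**Safeguards exist.** They do. Noise removal, normalization and rejection of clips with environmental noise reduce the problem, and SHAP may hint at a non-cardiac feature. None of them compares settings, so none tests for the shortcut.

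**Aim 2 is the proper test.** An independent consecutive cohort with echocardiography as reference would expose a gross shortcut. What remains is an optimistic Aim 1 and possibly a wasted validation. A partial loss would be harder to see: the plan's sample size there rests on about 19–20 cases.

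**The detail may be elsewhere.** The full protocol is a supplement that was not available and may already cover this.

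Four stronger readings are tempting but unsupported:

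- *A model that merely recognises the NICU could meet the targets.* That would need more than 95% of SHD newborns and fewer than 10% of controls to be recorded there. Nothing suggests this, and the background-only rows in step 4 stay below 95% sensitivity.
- *Ventilator noise is a cue.* The acquisition rules specify spontaneous breathing.
- *Centre and age are confounded with the label.* No per-centre ratio is given, and both groups share the window from 7 to under 30 days. Imbalance is possible but not shown.
- *Validation takes place in one setting, where the cue is absent.* The Validation phase includes a high-risk subgroup, and no text restricts where its recordings are made.

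**Conclusion.** The point holds in limited form. The article aligns recruitment stream with label, leaves recording setting unbalanced between the groups, selects features by their correlation with the label, and evaluates only inside that pool. If setting differs by label and leaves a trace after denoising, Aim 1 accuracy would be overstated and no stated analysis would reveal it.

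The size cannot be computed from the documents. Under the assumed shares, setting alone is worth an AUC of 0.625 to 0.80. The conclusion rests on two assumptions: that NICU recordings come mainly from newborns with SHD, and that some background difference survives preprocessing. The harm is an over-optimistic Aim 1 and late discovery in Aim 2, not an undetected error in the final validation result. This calls for an inexpensive improvement to the stated evaluation; it does not invalidate the design.

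**What to change.** 1. Log recording setting, centre and age in days with each wav file.
2. Where feasible, enrol both groups at every centre, with overlapping age and setting.
3. Before the model is frozen, report:
   - the AUC of a model that uses only setting, centre and age, as a benchmark the sound model must exceed;
   - performance restricted to newborns recorded in the same setting, for example outpatients only;
   - leave-one-centre-out performance beside the planned k-fold results. This does not by itself remove a setting effect that is present in every centre, so it complements the same-setting analysis and does not replace it.

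**Cost.** A few data fields and some extra analysis on the same 600 newborns. Headline internal accuracy may fall. Subset estimates are less precise: if 60% of SHD newborns were recorded in the NICU (assumed), 400 × 0.40 = 160 would remain for an outpatient-only sensitivity. The half-width would be 1.96 × √(0.95 × 0.05/160) = 0.034, against 0.021 for all 400. If 30% were recorded there, 280 would remain and the half-width would be 1.96 × √(0.95 × 0.05/280) = 0.026.

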#### Derivation phase

After screening of eligible patients, written informed consent will be obtained from parents or caregivers.

The first echocardiographic evaluation will take place at a post-natal age < 30 days. Age at recording and echocardiographic evaluation will be planned not before 7 days of post-natal life to allow completion of proper cardio-circulatory transition in the healthy newborns (i.e. ductal closure, pulmonary vascular remodelling, foramen ovale physiologic shunt). The echocardiogram will be linked to an anonymous identifier which will be used to link the exam to the patient without breaching patient privacy. The examination will be digitally stored and transferred to the Echocardiography Study Core Lab for formal revision. The cardiovascular neonatal status will be appropriately labelled as being with or without cardiovascular abnormalities.

Heart sound will be digitally recorded using as acquisition device Littmann Core Stethoscope (Eko Software) (3 M Company, Minnesota/USA). Cardiac sound tracings will be recorded and stored in wav format and encrypted transferred to the Bioengineer Research Unit for further elaboration. Cardiovascular neonatal status will be un-blinded to the Bioengineer Research Unit to allow for proper handling of classifier training.

The details of the acquisition method are as follows:

Acquisition device: Littmann Core Stethoscope (Eko Software) (3 M Company, Minnesota/USA)No filtering of raw signal will be applied. Specifically, the Stethoscope filtering and volume equalization will be set at 0 through the Eko interface. The only residual filter will be the analogue filter related to the stethoscope membrane's elastic properties. This is to minimize the impact of the specificities of the Eko Software on the sound samples and therefore on the training of the classifier.Position of the auscultation: mid precordium, 1 cm medial and 1 cm above papilla mammae (see Online Supplementary Material). Gentle pressure is applied on chest, spontaneous breathing, patients will be kept as calm as possible using maternage without any sedation. Sound sampling will be performed in a calm environment (outpatient clinic or neonatal intensive care unit). A total of three recordings per patient are anticipated to improve sound quality. Sampling tracings with abnormal acoustic contamination (intense crying, environmental noises, friction rubs) will be discarded.Average recording duration: 15 s

We specifically opted for a real-life cardiac auscultation to train the classifier to work in clinically representative setting. The neonate will be handled with maternage and comfortable measures, but no sedation will be used. The clip duration is based on survey data (unpublished) reporting that average neonatal cardiac auscultation in clinic is roughly between 10 and 20 s. Average heart rate in neonate is about 130 beats per minute, as a consequence, 15 s duration clip will record about 30 cardiac cycles. To enhance standardization of recording procedure, we opted for a single recording focus located at the level of mid-precordium (see Figure Online Supplementary Material).

Phonocardiographic signals will be stored as wav files in an encrypted cloud system to be transferred for further analysis (*Graphical abstract*). Tracings will undergo preliminary processing to remove background noise, and will be segmented to generate sound samples of homogeneous suitable tuned duration. As the last step of the preprocessing, the filtered records will be normalized for preventing inhomogeneity in the extracted features. Data analysis will be then implemented based on handcrafted feature extraction. The main objective of feature extraction is to identify a small number of representative features characteristic properties of a sound sample, that replace the high-dimensional raw signals still preserving its informative content with respect to the phenomenon under investigation. Relevant features are then fed to the classification algorithm to discriminate between healthy and abnormal subjects. Multiple different techniques will be used for feature extraction in sound signals, and can be loosely grouped into frequency-domain techniques, time-frequency domain techniques, linear predictive coding, and time-domain techniques. Each of these techniques provides descriptors of potentially relevant properties of the sound sample, which can be used as features or further processed to extract higher level characteristics of the signal (such as systole and diastole variability). To maximize the robustness of our results to less-than-ideal acquisition conditions, we will train the classifiers using features from all the above-mentioned domains and will perform a feature selection procedure to select those features which are mostly correlated to the outcome of interest. Standard machine learning models will be preferred, as simpler models tend to perform more robustly when training data is limited. Neural networks may be implemented if they will exhibit superior results with respect to standard models on the available dataset without clear signs of overfitting. Following the standard best practice, the dataset will be split into training set, validation set and test data set. For evaluating the performance of classifiers, K-Fold cross-validation with different fold numbers will be used: 10-fold, 5-fold, and Leave-One-Out-Cross-Validation (LOOCV). In LOOCV, the number of folds is equal to number of records. Gini importance for Random Forest classifiers will be used as a tool to validate parameters with least predictive contribution. Once a proper classifier has been trained a post training analysis to determine the most relevant features will be conducted. The purpose of this analysis is to investigate to which extent each feature is contributing to the selection of one class with respect to the other. Techniques for feature relevance estimation based on SHAP values, or permutation analysis will be applied also with the aim of providing a proper explanation to the model decision (*Graphical abstract*).

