Concordance/discordance pattern between patient-centred comparisons between digital and clinical screening results will be performed using the echocardiography as primary modality of outcome ascertainment (*Figure 1*). False positive will be defined healthy newborns receiving a ‘positive’ screening result using either the clinical (standard or face-to-face auscultation) or the digital approach. Similarly, false negative will be defined newborns with SHD receiving a ‘negative’ screening result using either the clinical (standard or face-to-face auscultation) or the digital approach.

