### Statistic plan

Between-group comparisons for clinical and outcome variables will be performed using independent samples *t*-test, Wilcoxon rank sum test, chi-square analysis, or Fisher's exact test using appropriate variable-specific denominators.

For experimental design Aim 1, limited data are available to build up a reliable power calculation at this stage, but we expect to enrol 600 patients with 2:1 diseased:healthy newborn ratio in this experimental phase. The rationale behind the ratio is due to the higher variability of diseased subjects with respect to the healthy ones.

Specific potential classifiers will be studied in the spectral features, cepstral features, and time-domain features. Dataset will be split into training set, validation set, and test data set. The performance of the classifiers will be evaluated using K-Fold cross-validation. Different folding levels will be tested: 10-fold, 5-fold, and LOOCV, aiming for >95% sensitivity and >90% specificity. The numerosity of the sample we target will allow to estimate the target sensitivity and specificity with sufficient accuracy, in particular with the target numerosity we can estimate a 95% confidence interval of ±2% in the sensitivity estimate and ±4% for the specificity estimate.

Gini importance for Random Forest classifiers will be used as a tool to validate parameters with least predictive contribution. Gini importance can be defined as the probability of making a false classification of a randomly chosen record if it were randomly labelled in the class distribution. During the training of the decision trees of the random forest, each tree is a set of internal nodes and leaves. In the internal node, selected feature is used to make decision of dividing the dataset into two separate splits. Selection of the feature is done with Gini impurity criterion. The feature that brings the highest decrease of Gini impurity is selected for the internal nodes. Even after training, how each feature decreases the impurity can be calculated and accepted as the importance of that feature.

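### Aim 1 mixes units: leave-one-out cross-validation is by record, but the stated precision and Aim 2 are by newborn, so meeting the accuracy target per record need not mean meeting it per newborn

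*Protocol article*

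**What the plan says.** **Recordings (Study procedure, Derivation phase).** The article states: "A total of three recordings per patient are anticipated to improve sound quality". It adds: "Sampling tracings with abnormal acoustic contamination (intense crying, environmental noises, friction rubs) will be discarded". The number of usable tracings can therefore differ between newborns. Tracings "will be segmented to generate sound samples of homogeneous suitable tuned duration", so one recording may give several samples.

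**Cross-validation (same section).** 10-fold, 5-fold and leave-one-out cross-validation are planned. Only the last has a stated unit: "In LOOCV, the number of folds is equal to number of records". The same paragraph describes the purpose by person: "Relevant features are then fed to the classification algorithm to discriminate between healthy and abnormal subjects".

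**Target and precision (Statistic plan).** The article says "we expect to enrol 600 patients with 2:1 diseased:healthy newborn ratio in this experimental phase". The cross-validated performance is judged against a target, "aiming for >95% sensitivity and >90% specificity", with 95% confidence limits of ±2% for sensitivity and ±4% for specificity.

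**Validation (Study procedure, Validation phase).** Aim 2 rests on "patient-centred comparisons between digital and clinical screening results", and false positives and false negatives are defined as newborns. Recordings of 15 s are acquired, with no number per newborn.

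**The concern.** Sensitivity and specificity depend on what is counted. If each tracing is a case, a newborn with three tracings counts three times and can be right on two and wrong on one. If the newborn is the case, there is one result, and the way the tracings are merged becomes part of the test.

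The article ties one target to an evaluation that is, for leave-one-out, explicitly by record. It supports that target with a precision figure that fits newborns, and then validates by newborn. Two things are at stake. First, the Aim 1 decision that the classifier is good enough could rest on a figure that does not predict the Aim 2 quantity. Second, the merging rule moves the operating point. If it is not fixed as part of the classifier, sensitivity can later be traded for specificity, and this would carry into net classification improvement and the Aim 3 counts of avoided and missed examinations.

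Leaving out one record at a time also keeps the same newborn's other tracings in the training data. That is a separate reason to keep each newborn whole within a fold, and it is not quantified here.

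**Working it through.** **Inputs from the article.** 600 newborns at 2:1, so 400 diseased and 200 healthy. Target boundary: sensitivity 0.95, specificity 0.90. Three recordings per newborn in the derivation phase.

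**Assumptions.** All three recordings are usable. Record-level performance is exactly 95%/90%. The within-newborn correlation ρ of record results is not given, so a range is shown.

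**Step 1: the plan's own precision.** Half-width = 1.96 × √(p(1 − p)/n).

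- Newborns: 1.96 × √(0.95 × 0.05/400) = ±2.14%, and 1.96 × √(0.90 × 0.10/200) = ±4.16%. These round to the stated ±2% and ±4%.
- Independent records, three each (n = 1,200 and 600): ±1.23% and ±2.40%. These do not match.
- Records with a clustering allowance, dividing n by 1 + 2ρ: ρ = 0.5 gives ±1.74% and ±3.39%, which does not match. ρ = 0.8 gives ±1.99% and ±3.87%, which would round to the stated figures. The article mentions no such allowance, so 400 and 200 newborns is the natural source.

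**Step 2: from record to newborn.** For ρ = 0, the number of positive records out of three is binomial. For ρ > 0, it is beta-binomial with a = p(1 − ρ)/ρ and b = (1 − p)(1 − ρ)/ρ, where p is the probability that a record is positive (0.95 if diseased, 0.10 if healthy).

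Worked case, ρ = 0.5, so a + b = 1:

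- Diseased, all three positive: 0.95 × 1.95 × 2.95 / (1 × 2 × 3) = 0.911. This is the all-positive sensitivity.
- Diseased, none positive: 0.05 × 1.05 × 2.05 / 6 = 0.018, so any-positive sensitivity is 0.982.
- Healthy, none positive: 0.9 × 1.9 × 2.9 / 6 = 0.8265. This is the any-positive specificity.
- Healthy, exactly one positive: 3 × 0.1 × 0.9 × 1.9 / 6 = 0.0855, so majority specificity is 0.8265 + 0.0855 = 0.912.
- Healthy, all three positive: 0.1 × 1.1 × 2.1 / 6 = 0.0385, so all-positive specificity is 0.9615.

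Newborn-level sensitivity / specificity:

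| ρ (assumed) | Any positive | Majority | All positive |
|---|---|---|---|
| 0 | 99.99% / 72.9% | 99.3% / 97.2% | 85.7% / 99.9% |
| 0.2 | 99.6% / 77.3% | 97.3% / 93.8% | 88.2% / 98.9% |
| 0.5 | 98.2% / 82.7% | 95.7% / 91.2% | 91.1% / 96.2% |
| 0.8 | 96.4% / 87.2% | 95.1% / 90.2% | 93.5% / 92.6% |

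**Step 3: newborns whose records disagree.** Healthy: 27.0%, 13.5% and 5.4% at ρ = 0, 0.5 and 0.8. Diseased: 14.3%, 7.1% and 2.9%.

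In every row, any-positive misses the 90% specificity target, all-positive misses the 95% sensitivity target, and majority meets both, narrowly at ρ = 0.8.

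**The case against.** The strongest reply is that Aim 1 is meant to be by newborn throughout. Only leave-one-out is explicitly by record. The 10-fold and 5-fold units are not stated, the classifier is said to separate subjects, and the precision figure fits newborns. This stands. A reader might infer that the whole of Aim 1 is scored by record, and the article does not support that. What remains is that one stated evaluation rule disagrees with the rest.

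Second, three recordings are mentioned only for derivation, and the purpose given, better sound quality, could mean repeat takes from which the best is kept. The article does not say so, and a retained tracing may still be cut into segments. It is fair, however, that three separately scored recordings per validation newborn cannot be assumed.

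Third, the combining rule may be in the full protocol, which the article places in its online supplement and which is not shown here. A reader might infer that newborns with disagreeing recordings cannot be scored at all. That does not follow, because the rule is only absent from a condensed article, and its absence alone is not the point.

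Fourth, the effect depends on an assumed correlation. Independence gives the most dramatic spread (specificity from 73% to 99.9%) but is implausible for repeat recordings of one infant at one fixed site. At ρ = 0.8 the spread is much smaller. This is accepted, and the conclusion uses ρ = 0.5 to 0.8.

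Finally, nothing in the article says that the rule would be chosen after the validation data are seen. That is a risk to close off, not a stated plan.

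**Conclusion.** The point holds as an inconsistency of unit within Aim 1 and between Aim 1 and Aim 2. Leave-one-out by record, run as written, gives performance on a unit that matches neither the natural reading of the article's precision figure nor its Aim 2 endpoints.

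With three usable records at exactly 95%/90% each and an assumed ρ of 0.5 to 0.8, newborn-level specificity lies between about 83% and 96% and sensitivity between about 91% and 98%. Per 1,000 healthy newborns at ρ = 0.5, that is about 174 false positives under any-positive, 88 under majority and 39 under all-positive (1,000 × one minus specificity).

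A reader might infer that the target fails to carry over whatever is done. The figures do not support that, since a majority rule keeps both targets at every correlation computed. The right statement is that the target need not carry over, and that this depends on a rule not stated in the article. The change is worth making before Aim 1 is analysed, and it does not put the design in doubt.

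**What to change.** 1. Replace leave-one-out by record with evaluation by newborn: keep all recordings and segments of a newborn in the same fold, for 10-fold, 5-fold and leave-one-out alike and for the training, validation and test split, and produce one result per newborn.
2. State that the >95% sensitivity and >90% specificity target is assessed on those newborn-level results.
3. Treat the rule that turns usable recordings and segments into one result as part of the classifier, for example the mean score over all usable segments with one threshold. A majority vote or a pre-specified choice of the best tracing would also serve. The rule should cover newborns who lose tracings to the discard rule, including a tie when two remain and the case when none remain.
4. Lock the rule and threshold before the first validation newborn is classified, and use the same rule in Aim 2.

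**Cost.** A few sentences of text and a small change in code, with no extra recruitment or recordings. Aim 1 estimates rest on 400 and 200 newborns instead of a larger number of records, but the ±2% and ±4% already correspond to those numbers, so the stated precision is unchanged.
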